| [name] | Wonkang University College of Korean Medicine | | Assistant professor | | [name] / [[contact]](mailto:[contact]) | | Study design and data analysis consultatio | |
| [name] | Wonkang University College of Korean Medicine | | Graduate student  (Master’s) | | [name] / [[contact]](mailto:[contact]) | | Assist in study design and data analysis | |

1. Roles by affiliation

* Kyung Hee Bi,Che,Dam Korean Medicine Clinic: recruit participants, collect informed consent, perform trial

* Korean Institute of Oriental Medicine: study design and analysis, monitoring, administration

* Wonkang University College of Korean Medicine: study design and data analysis consultation

1. Name and address of trial facility

Trial facility (single-center study): Kyung Hee Bi, Che, Dam Korean Medicine Clinic ([name])

1. Sponsor

National Institute for Korean Medicine Development ([name])

1. Study period

Anticipated study period (1 year from approval by joint IRB. Scheduled to be completed on August 31, 2024)

1. Study participants
2. Recruiting facility

(Single-center) Kyung Hee Bi, Che, Dam Korean Medicine Clinic

1. Number of patients to be recruited

After screening candidates for eligibility, 30 participants who received mSMS will be recruited.

Study participants must meet all of the inclusion and not meet all of the exclusion criteria to be enrolled in the study.

1. Inclusion criteria
2. Adult men and women aged 19–74 years.
3. BP measured from the reference are at time of screening:

- If not taking antihypertensive drugs: 140 mmHg ≤ MSSBP(mean sittingSBP) < 180 mmHg
- If taking antihypertensive drugs: 130 mmHg ≤ MSSBP(mean sitting SBP) < 180 mmHg

1. Voluntarily provide a fully informed consent to provide medical records and personal information for use in the study.

- (*Reference arm is selected based on the process outlined in “12. Observation parameters-B.Measurement items”)
- (*Mean seated BP is defined in “12. Observation parameters-B.Measurement items)

1. Exclusion criteria
2. ≥ 20 mmHg difference in Systolic Sitting Blood Pressure (SSBP) and more than a 10 mmHg difference in Diastolic Sitting Blood Pressure (SDBP) across three consecutive measurements, taken at least 2 minutes apart in both arms
3. Mean seated SBP (MSSBP) ≥ 180 mmHg or mean seated DBP (MSDBP) ≥ 110 mmHg in the reference arm at time of screening

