- The study is conducted under a national research and development project commissioned by the National Institute for Korean Medicine Development (NIKOM) (evidence-generating research as part of Korean medicine innovative technology development project). The research data collected according to the study announcement will be recorded and stored through E-CRF (Mytrial) established by NIKOM and provided to them. Provision of the study data to a third party and use of the data for secondary studies will be permitted only after obtaining a separate consent from from the participants for the purpose.

1. Method
2. Outline of method
3. Study period

Anticipated study period (1 year from approval date. Scheduled to be completed by August 31, 2024)

1. Study site

Kyung Hee Bi, Che, Dam Korean Medicine Clinic; a prospective observational study on patients

1. Study design

Single-group, prospective, exploratory, preliminary observational study

This study is an observational study for preliminary exploration of the therapeutic effects of modified SMS on HTN and for exploration of feasibility for future randomized controlled trial.

1. Study schedule (standard management protocol): 4 clinical assessments

Baseline (wk 0, screening and enrollment, visit 1)

Mid-treatment (4 weeks after beginning dosing of modified SMS) (visit2)

End of treatment (8 weeks after beginning dosing of modified SMS) (visit3)

4-week f/u after treatment (12 weeks after beginning dosing of modified SMS) (visit4)

1. Standard protocol for modified SMS

The participants will undergo the following process per the standard protocol:

When using modified SMS, those receiving any other KM treatments, including acupuncture, pharmacopuncture, and moxibustion, will be excluded

1. Standard herbal medicine prescription protocol

- Compliance with pre-visit instructions:
  After making an appointment for the visit, patients are instructed to fast for 8 hours before the visit, refrain from smoking, drinking, and consuming caffeine the day before the visit, and to visit the clinic between 8–12 AM.
- History taking
- 3D BP waveform test (3-d pulse imaging study), blood test
- Same tests performed at F/u on weeks 4, 8, and 12 after herbal medicine prescription

1. Standard protocol visits

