       2. Measurement items: Aspatate transaminase(AST), Alanine transaminase(ALT), Gamma glutamyl peptidase(GGT), Total Bilirubin, BUN, Creatinine, Total cholesterol, Glucose
       3. Measurement method

- Refrain from caffeine, alcohol, and tobacco consumption the day before the test
- 8-hour fasting is required before the test; water allowed
- Test takes 10 minutes

1. [**3D Blood pressure and pulse wave test]**: **3d pulse wave imaging device (3D MAC, ㈜ Daeyomedi Co., Ltd., South Korea)**: 10 minutes ( See [Attachment 1])
   - - 1. Pulse strength value and stage (Unit:gf)
       2. Pulse depth value and stage (Unit:gf/cm^2)
       3. Pulse velocity value and stage (Unit:beats)
       4. Pulse shape value and stage (Unit:step)
       5. Radial artery augmentation index(R-AI) (Unit:%)
       6. SBP (Unit:mmHg)
       7. DBP (Unit:mmHg)
       8. Pulse pressure (PP) (Unit:mmHg)
       9. Pulse rate (PR) (Unit:beats/min)
       10. Cardiac output (1 beat) SV (Unit:mL/beat)
       11. Cardiac output (1 minute) CO (Unit:L/min)
       12. Systemic vascular resistance index(SVRI) (Unit:dyn*s/cm^5/m^2)
2. European Quality of Life Five Dimension Five Level Scale (EQ-5D-5L) questionnaire: 5 minutes ( see [Attachment2] )
3. Other

Adverse events and concomitant treatments are monitored per patient’s report and questions at every visit

1. Outcome measurement criteria and method
2. Primary outcome

This study is an exploratory observational study aiming to explore the safety and BP-lowering effetcs of modified SMS prepared and prescribed by Kyung Hee Bi, Che, Dam Korean Medicine Clinic for patients with HTN by comparing SBP before and after treatment.

1. [Changes in MSSBP] use Omron Healthcare HEM-9000AI
   Amount of change in MSSBP at end of treatment (visit 3) compared to the baseline (visit 1)
   - - 1. Null hypothesis (H0): There is no difference in MSSBP between the baseline (Visit 1) and end of treatment (visit 3).
       2. Alternative hypothesis (HA): There is a difference in MSSBP between the baseline (Visit 1) and end of treatment (visit 3).
2. Secondary outcome
3. Amount of change of MSSBP at visit 2 compared to the baseline (visit 1)
4. Amount of change of MSSBP at visits 2 and 3 compared to the baseline (visit 1)
5. Percentage of participants with normalized BP: percentage of patients who achieved normal BP compared to MSSBP/MSDBP measured at each time point (percentage of patients who had a BP of less than 140/90 mmHg at end of treatment)

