6. BP response rate at end of treatment (visit 3) compared to the baseline (visit 1) (percentage of patients who had MSSBP drop by 20 mmHg or more or MSDBP drop by 10 mmHg or more)
7. Amount of change in individual parameters on 3D pulse wave imaging at visits 2 and 3 compared to the baseline (visit 1)
8. Amount of change in EQ-5D-5L score at visits 2 and 3 compared to the baseline (visit 1)
9. Outcome evaluation criteria

This study is a prospective study conducted to present data for subsequent studies on modified SMS; the purpose is not to determine the clinical efficacy of the drug, but rather, to explore and collect preliminary data.

However, for the statistical analysis in this study, we will present the degree of improvement in the continuous variables using descriptive statistics.

Efficacy is determined based on the improvement of MSSBP, 3D pulse wave imaging parameters, and Eq-5D-5L score at visits 2 and 3 compared to the baseline, and the percentage of patients who have achieved such improvements is presented. However, because the study is an exploratory study without a control group, there are limitations in determining efficacy.

As this study observes effects during a routine treatment protocol, we will collect the following data that may potentially influence BP and control for them in the analysis.

* Collection of information about the use of antihypertensive drugs.
* If the patient is using antihypertensive medication, they are informed to notify the investigator upon changes in the dose and dosage of the drug.
* Patients are informed to maintain their normal lifestyle, including exercise and diet

ANCOVA is performed with sociodemographic variables that may affect HTN, namely sex, age, BMI, duration of HTN, comorbidity, BP at initial visit, use of antihypertensive medication, and types of drugs, controlled for as covariates.

1. Anticipated AEs, precautions, and measures to address them
2. Additional AEs anticipated as a result of participation in observational study

In this observational study, the same process used in the standard treatment protocol is used, which involves taking modified SMS, performing tests and questionnaires, and documenting them in the CRF. Thus, there are no additional tests or interventions performed other than those included in the standard treatment process; for this reason, there are no other anticipated AEs in addition to the AEs that may occur during the standard treatment process.

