Full Analysis Set(FAS): Per the Intention-to-Treat (ITT) principle, FAS includes participants who have received the herbal medicine preparation at least once and have had at least one measurement of the primary outcome measure

Safety Set (SS): Includes participants who have received the herbal medicine preparation at least once and have had at least one safety-related f/u

For demographic and baseline data, categorical data will be presented as n (%), and continuous data will be presented as mean±SD.

For efficacy parameters, continuous variables will be analyzed with paired t-test or Wilcoxon signed rank test, and categorical variables will be analyzed using the McNemar test or McNemar Exact test depending on their normality.

For safety parameters, adverse drug reactions (ADRs), SAEs, and serious ADRs will be presented as n (%), and differences across time points will be analyzed using the McNemar test or McNemar Exact test.

ANCOVA model will be used for analysis with sociodemographic factors that may affect HTN, such as sex, age, and use of antihypertensive drugs, included as covariates.

1. Withdrawal of consent and discontinuation
2. Discontinuation criteria

Participants may be discontinued from the trial in the following instances:

- Participants or their legal representatives requests discontinuation or participant withdraws consent due to unsatisfactory treatment effects during the study period
- Violation of inclusion criteria or meeting exclusion criteria
- Failure to take the modified SMS even once during the observational study period, despite giving consent and meeting eligibility criteria
- Occurrence of SAE related to the herbal medicine or AE making continuation in the study difficult
- Change of prescription during study
- Participant’s violation of study plan
- Lost to f/u during study period
- Other reasons due to which continuation of study is deemed inappropriate by the investigator

1. Study termination criteria

Upon occurrence of SAE suspected to be caused by the investigational drug, the PI notifies the joint IRB within 24 hours and terminate the study.

The clinical trial may be terminated prematurely in the following cases:

- Harmfulness of investigational product is discovered
- Moderate or severe AE deemed to have a relationship with the clinical trial occurred in more than 25% of the entire study population
- Study poses threat to the safety and well-being of study participants

1. Withdrawal of consent

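### The normalised-BP rate counts treated patients already below 140/90 at entry; its McNemar test tilts towards improvement as the untreated share rises, and the response rate has no baseline pair

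*Protocol*

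**What the plan says.** **Endpoints (Protocol, Section 13, Secondary outcome).** Normalised BP is the "percentage of patients who had a BP of less than 140/90 mmHg at end of treatment". The BP response rate, visit 3 against visit 1, is the "percentage of patients who had MSSBP drop by 20 mmHg or more or MSDBP drop by 10 mmHg or more".

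**Entry rules (Protocol, Inclusion and Exclusion criteria).** For untreated patients: "If not taking antihypertensive drugs: 140 mmHg ≤ MSSBP(mean sittingSBP) < 180 mmHg". For treated patients: "If taking antihypertensive drugs: 130 mmHg ≤ MSSBP(mean sitting SBP) < 180 mmHg". Diastolic pressure has only an upper bound, through the exclusion of "mean seated DBP (MSDBP) ≥ 110 mmHg in the reference arm at time of screening".

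**Baseline (Protocol, Study schedule).** One visit serves for selection and for baseline: "Baseline (wk 0, screening and enrollment, visit 1".

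**Test (Protocol, Section 16, Data analysis and statistical methods).** For efficacy, "categorical variables will be analyzed using the McNemar test or McNemar Exact test depending on their normality". Tests are two-sided at 5%, missing efficacy values are filled by LOCF, and there is no control group.

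**The concern.** A normalisation rate should describe people who had something to normalise. Here the operational definition looks only at the end of treatment, while the lower entry limit for treated patients lies 10 mmHg below the success threshold. Part of the rate can therefore be present before the first dose.

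The paired test has a different weakness. An untreated participant is above the threshold at visit 1 by eligibility, so any ordinary visit-to-visit fall below 140/90 counts as improvement, and no untreated participant can supply the opposite change.

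The response rate fits McNemar worse still, because response is already a comparison with baseline.

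The study is meant to supply data for later work, including a randomised trial. A rate that contains already-controlled patients, or a p-value helped by the entry cut, could be carried into that planning.

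**Working it through.** **1. The plan's own figure.** The sample size is 20 evaluable participants with 33% dropout: 20 / (1 - 0.33) = 29.85, rounded up to 30. This agrees with the protocol, so n = 20 and n = 30 are used below. The protocol gives no expected normalised rate to reproduce.

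**2. Who can be below 140/90 at visit 1.**
- Untreated: systolic is at least 140, so nobody.
- Treated: systolic 130-139 with diastolic below 90 is admissible. A treated patient at 135/80 at visit 1 and 135/80 at visit 3 meets the success definition without any change.

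This step needs no assumption.

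**3. Size under no effect.** The protocol gives no BP distribution, so these inputs are assumed: population mean systolic 140 or 145 mmHg, between-person SD 12; mean diastolic 84, SD 8; systolic-diastolic correlation 0.5; independent visit-to-visit noise with SD 0, 6, 8 or 10; treated share 0, 50 or 100%. Each simulated person is selected on the visit 1 reading by the protocol's rules and keeps the same true BP at visit 3 (10,000 samples per setting).

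With essentially no visit noise, an all-treated sample shows a rate of 23-32%, all of it already normal at entry. With visit SD 6-10:

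| Treated share | Rate below 140/90 at visit 3 | Mean count, normal to not normal | Samples with that cell empty | Significant favourable, n = 20 | Significant favourable, n = 30 |
|---|---|---|---|---|---|
| None | 12-23% | 0 | 100% | 3-29% | 16-69% |
| Half | 18-27% | 0.9-1.7 | 16-39% | 1-8% | 4-19% |
| All | 23-31% | 1.7-3.5 | 2.5-16% | 0.2-1.8% | 0.9-3.7% |

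**4. How much of the rate was there at entry.** Take mean 140, visit SD 8, all treated, n = 20. The no-effect rate is 30.7%, or 6.14 people. Of these, 2.98 crossed from not normal to normal. The other 6.14 - 2.98 = 3.16, about half, were below 140/90 at both visits. Restricted to those not below 140/90 at visit 1 (27.1% were), the rate is 2.98 / [20 × (1 - 0.271)] = 2.98 / 14.58 = 20.4%. With half treated, the rate goes from 25.0% to 3.42 / [20 × (1 - 0.135)] = 3.42 / 17.3 = 19.8%.

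**5. The McNemar test.** Let b be the number going from not normal to normal and c the number going from normal to not normal. The exact test is binomial on b + c with probability 0.5. For untreated participants c = 0 by eligibility. In a sample with c = 0, p = 2 × 0.5^b: b = 5 gives 0.0625 and b = 6 gives 0.031. The last two columns of the table apply the exact test to the pooled sample. If all are untreated, an unfavourable result is impossible. With no visit noise nobody crosses and there are no false positives. So the tilt comes from regression to the mean acting on a one-sided entry cut, not from the empty cell alone.

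**6. The response rate.** Response is a drop of a stated size from visit 1 to visit 3: one yes/no value per person. There is no response state at visit 1, so no 2 × 2 table against baseline can be formed.

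**The case against.** **The pooled table is not empty by design.** A reader might infer that eligibility empties one McNemar cell for the whole trial. It does not. The protocol plans no untreated-only test, and the treated entrants already below 140/90 are exactly the people who can fill the reverse cell; those who stay normal are concordant and add nothing to the test. The two weaknesses also peak in opposite samples: the rate is most inflated when all are treated, and there the test's false-positive rate is below 5%. This objection stands, and it is why the test is described as tilted in proportion to the untreated share.

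**The large error rates are a corner case.** Figures up to 69% need every participant untreated and 30 fresh visit 3 readings. The protocol requires neither, and it expects 67% to return at week 4. If LOCF carries a baseline forward, an untreated participant cannot cross, while a treated participant normal at entry stays normal. This stands too.

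**Safety comparisons.** A reader might infer that McNemar is also impossible for adverse events. The text says only that "differences across time points will be analyzed using the McNemar test or McNemar Exact test", without naming baseline, and Table 2 records adverse events at visits 2, 3 and 4. Pairing between those visits is possible, so no finding is made there.

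**Wording and scope.** The endpoint's main clause speaks of achieving normal BP, which could imply a change of state, and denominators are often left to an SAP. But the operational definition in brackets is in the protocol and has no baseline condition. The normality phrase in the test sentence has no meaning for binary data; it probably belongs to the choice between t-test and Wilcoxon and changes nothing here.

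**Exploratory status.** The protocol says that it does not aim to establish efficacy and acknowledges the limits of having no control. That lowers the weight of the point. It does not warn that the rate may include people already below the threshold.

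**Conclusion.** The point holds in three limited parts.

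- **Rate:** certain from the text. Treated patients already below 140/90 at visit 1 can count as normalised. The size, roughly 23-32% with no effect in an all-treated sample, rests on the assumed distributions.
- **Test of normalisation:** tilted towards improvement to the extent that participants are untreated. With no effect, a significant favourable result occurs in about 0-4% (all treated), 1-19% (half treated) and 3-69% (none treated) of samples across n = 20 to 30. The actual treated share is not known from the protocol. It cannot be concluded that the pooled test would reject mainly because of eligibility.
- **Response rate:** McNemar against baseline cannot be applied. This needs no assumption.

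These are secondary endpoints of an exploratory single-group study; the primary outcome is not touched by this point. The correction is worth making because it removes a built-in inflation at little cost.

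**What to change.** In the Secondary outcome and Data analysis sections:

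1. Compute the normalised-BP rate only among participants with MSSBP ≥ 140 or MSDBP ≥ 90 mmHg at visit 1.
2. List treated entrants already below 140/90 at visit 1 separately, with their status at visit 3.
3. Report normalisation and response as n/N with an exact 95% confidence interval, and drop the McNemar p-value against baseline for both. Once the denominator is restricted, the reverse cell really is empty by construction, so a proportion with an interval is the fitting summary.
4. State next to these rates that regression to the mean remains, because selection and baseline use the same reading. In the worked setting the restricted rate is still about 20% with no effect.

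The cost is analysis wording only, with no new data. The denominator becomes smaller, the interval wider, and the normalised rate less favourable.

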4. Liver disease or kidney disease requiring treatment
5. Secondary hypertension
6. History of severe CVD: e.g., myocardial infarction, angina, severe arrhythmia
7. Diagnosis of psychiatric disorder or treatment for psychiatric disorder, including depression, within 2 months of visit
8. Other reasons that contraindicate use of modified SMS as determined by the clinician

- (*Reference arm is selected based on the process outlined in “12. Observation parameters-B.Measurement items”)
- (*Mean seated BP is defined in “12. Observation parameters-B.Measurement items”)

1. Control group

A prospective single-group preliminary observational design; there is no control group, and blinding and randomization are not applicable.

1. Anticipated sample size and grounds for sample size determination

This is an exploratory preliminary prospective observational study. In general, preliminary studies require a minimum of 12 participants [9]. In the present study, we aim to obtain data from 30 participants.

F/u is performed every 4 weeks. In general, 67% of participants re-visit the facility on week 4.

To obtain data from 20 participants with a potential 33% dropout rate, **30 participants** are required.

Every month, about 10 patients take modified SMS, so recruiting the target sample size within the study period is feasible.

In preliminary studies, a minimum of 12 participants are generally required. **Given that this study is a preliminary study collecting exploratory data for subsequent studies, as opposed to a study investigating the therapeutic efficacy, recruitment of 30 participants in consideration of potential dropouts is deemed adequate.**

1. Participant recruitment

Participants will be recruited among patients who visit the Kyung Hee Bi, Che, Dam Korean Medicine Clinic and based on the clinician’s assessment and patient consent.

To ensure consistency of recruitment and fairness for potential participants, a recruitment announcement containing the overall information about the study, including its purpose, inclusion and exclusion criteria, and study schedule, will be posted on the bulletin board within the clinic for a specified period. Visitors to the healthcare facility interested in participating in the study can contact via the contact details listed in the announcement or by directly contacting the research team (PI and co-investigators).

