- Dose per pack: modified SMS: each pack contains 60 mL containing Pueraria lobata (5.33g), Platycodon grandiflorus (5.33g), Ophiopogon japonicus (5.33g), Dioscorea opposita (2.67g), Coix lacrymajobi (2.67g), and Schisandra chinensis (2.67g) (total 24g; unit g/day).
- Dosage: oral; 2 packs a day
- Treatment period: 8 weeks (56 days) (f/u every 4 weeks)
- Permitted concomitant treatments: Given the observational nature of this study, we will not limit any concomitant treatments and medications while undergoing the SMS regimen, and concomitant treatments will be documented.
  * Use/non-use of antihypertensive drugs will be documented.
  * If antihypertensive drugs are being used, patients are informed to notify the investigator upon changes in the dose and dosage of the drug.
  * Patients are informed to maintain their normal lifestyle, including exercise and diet.
- The dose and dosage of modified SMS used in this trial are identical to those used in actual practice at Kyung Hee Bi, Che, Dam Korean Medicine Clinic.

|  | | |
| --- | --- | --- |
| [figure not shown] | [figure not shown] | [figure not shown] |
| Cold extraction | Vacuum concentration | Concentrate |

Figure 5. Preparation facilities at Kyung Hee Bi, Che, Dam Korean Medicine Clinic and appearance of concentrates

1. Additional interventions, visits, and tests required for study participation per the purpose

The Standard management protocol at Kyung Hee Bi, Che, Dam Korean Medicine Clinic involves performing 3D BP waveform test and blood tests on patients taking herbal medicines every four weeks. In the present study, only patients taking modified SMS were enrolled. **Thus, there are no additional interventions required for participation in this study**

**In case of an adverse event, f/u is needed until the adverse event is resolved. In such cases, additional visits may be necessary.**

In case of an adverse event, additional tests, such as kidney function test, liver function test, and complete blood count, may be performed.

1. Control group, randomization, blinding

This is a single-group study without a control group, so randomization and blinding are not applicable.

1. Summary of study timeline (anticipated duration, place, staff in charge, study procedure)

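### The one-arm ANCOVA cannot deliver the promised control for influences on BP, and neither covariate list has a term for on-study changes in antihypertensive dose

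*Protocol*

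**What the plan says.** Section 13, Outcome evaluation criteria, states an aim: "we will collect the following data that may potentially influence BP and control for them in the analysis". The items that follow are use of antihypertensive drugs, notification of changes in their dose, and advice to keep exercise and diet as usual. The same section then names an ANCOVA with a closed list of eight covariates: "namely sex, age, BMI, duration of HTN, comorbidity, BP at initial visit, use of antihypertensive medication, and types of drugs, controlled for as covariates".

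Section 16, Data analysis and statistical methods, mentions the ANCOVA again with an open list: "such as sex, age, and use of antihypertensive drugs, included as covariates". It also sets the main test for continuous efficacy variables (paired t-test or Wilcoxon signed rank test) and LOCF for missing values in the FAS.

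Three other statements matter:
- The Control group section says "there is no control group, and blinding and randomization are not applicable".
- Under permitted concomitant treatments, "we will not limit any concomitant treatments and medications while undergoing the SMS regimen"; such treatments are documented.
- Table 2 schedules the collection of changes in medication history at visits 2, 3 and 4.

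**The concern.** The primary outcome is the within-patient change in MSSBP from visit 1 to visit 3. In a one-arm pre-post study, that change mixes any effect of modified SMS with everything else that moved BP over eight weeks. One such influence is a start, stop or dose change of an antihypertensive drug. The protocol sees this and promises to deal with it in the analysis, but the method it names cannot do so, for two reasons. ANCOVA removes covariate imbalance from a comparison between groups, and there is only one group. The listed covariates are also patient characteristics or treatment status, and none records a change of dose during treatment.

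At stake is how an adjusted result would be read. A reader could take it as freed from concomitant therapy when it is not. The protocol says that its data are meant to inform subsequent studies, so that misreading could carry into their planning.

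**Working it through.** **Inputs from the protocol.** The sample size section says "In general, 67% of participants re-visit the facility on week 4" and plans as follows: "To obtain data from 20 participants with a potential 33% dropout rate". The number to recruit is 30. The study has one arm and eight named covariates (section 13) or three (section 16). LOCF applies in the FAS.

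**Step 1. Reproduce the planning figure.** 20 / (1 − 0.33) = 20 / 0.67 = 29.85, rounded up to 30. This agrees with the protocol, so about 20 participants with data is its own expectation. The FAS needs one dose and one measurement of the primary outcome, and LOCF fills gaps, so the analysed number may lie between 20 and 30.

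**Step 2. What the adjusted mean is in one arm.** Let y be the MSSBP change and x the covariates, fitted by least squares with an intercept. The residuals sum to zero, so mean(y) = b0 + b·mean(x). The prediction at the covariate means is the raw mean change, whatever the covariates are. If visit 3 MSSBP is the outcome and baseline MSSBP a covariate, the prediction at the means is the visit 3 mean. Subtracting the baseline mean again gives the raw change.

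This was also checked in 5,000 simulated one-arm data sets at each of n=20 and n=30, with eight covariates. The largest difference between adjusted and raw mean change was below 1e-13.

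**Step 3. Illustration with assumed values (none is in the protocol).** Assume no effect of modified SMS, a background fall of 5 mmHg, and 20% of participants with an antihypertensive increase worth 12 mmHg. The expected change is −5 − 0.20 × 12 = −7.4 mmHg. At n=20 the simulated raw and adjusted changes were both −7.4 mmHg, so none of the 2.4 mmHg was removed. The 95% CI half-width was 5.3 mmHg with and without the eight covariates.

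In general, the amount left in the estimate is the proportion changed times the mean effect of the change. With 10% to 30% of participants and 8 to 10 mmHg (again assumed), this runs from 0.10 × 8 = 0.8 to 0.30 × 10 = 3.0 mmHg. It would be a spurious fall if therapy was intensified, and a masked fall if it was reduced.

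**Step 4. Size of the model.** Residual df = n − 1 − p. Expected R-squared from unrelated covariates = p / (n − 1).

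| Covariates (1 df each) | n | Residual df | Patients per covariate | Expected noise R-squared |
|---|---|---|---|---|
| 8 (section 13) | 20 | 11 | 2.5 | 8/19 = 42% |
| 8 (section 13) | 30 | 21 | 3.75 | 8/29 = 28% |
| 3 (section 16) | 20 | 16 | 6.7 | 3/19 = 16% |
| 3 (section 16) | 30 | 26 | 10 | 3/29 = 10% |

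One df each is the minimum for the eight; comorbidity or drug type with several levels would use more. If drug type is coded with a level for no drug, the use variable is redundant with it: in a check with four type levels, the five design columns had rank 4.

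**Step 5. Match the aim to the lists.** Section 13 counts dose changes among the data to be controlled for. The eight covariates include use and type of antihypertensive drugs but nothing on change; the three in section 16 include use only. The data exist, since Table 2 collects medication changes at every visit after baseline.

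**The case against.** The strongest reply is that little hangs on this ANCOVA. The paired t-test or Wilcoxon test is the main analysis, the study is labelled exploratory, and section 13 admits that efficacy is hard to judge without a control group. A regression that describes which patients changed more is legitimate in such a study. All of this stands and limits the weight of the point. It does not rescue the promise of control: the paired test also leaves antihypertensive changes in the estimate, and the ANCOVA is the only adjustment offered.

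A statistical analysis plan might settle the outcome variable and the coding. Those choices alone would not supply a comparator. The use covariate is undated and might include on-study starts, but it would still miss a dose change. A change of prescription is a discontinuation criterion, and data of participants who meet such criteria are to be discarded. It is not clear that this covers antihypertensives, since changes to them are expected and only have to be notified.

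A reader might infer more than the document supports:
- **That the two lists contradict each other.** They do not. Section 16 gives examples, and all three are among the eight. The model is stated twice and left unfixed.
- **That the large model makes the primary result unstable.** Overfitting affects the individual coefficients. The mean change at the covariate means is unaffected, and the interval in step 3 was essentially the same.
- **That software defaults would shift the adjusted mean.** This presumes equal weighting of category levels, which the protocol does not state.
- **That far fewer than 20 would be analysed.** This would need the week 4 revisit rate to apply again at week 8, and LOCF to be ignored.

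**Conclusion.** The point holds. Followed exactly, the stated ANCOVA does not provide the control that section 13 promises: it has no group contrast to adjust, its adjusted mean at the covariate means is the raw mean change, and no covariate records an on-study antihypertensive dose change. The identity is algebra and rests only on a least-squares fit with an intercept. The model is also thin, with 11 residual df and 42% expected noise R-squared at n=20, and 21 df and 28% at n=30, assuming one df per covariate.

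The effect of altered antihypertensive therapy on the primary estimate cannot be sized from the protocol, and it may go in either direction. The figures in step 3 are illustrations. It would go too far to say that a fall in BP will be wrongly credited to modified SMS, because how many participants change therapy, and which way, is unknown. The change is worth making, but the defect does not invalidate the study.

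**What to change.** 1. In sections 13 and 16, stop describing the ANCOVA as controlling for influences on BP. Call it a descriptive model of which patients changed more. State one short covariate list, identical in both places and including baseline MSSBP.
2. Report the primary visit 1 to visit 3 MSSBP change with a 95% CI on all readings as collected, whether or not antihypertensive therapy changed.
3. Add a sensitivity analysis of the same change, restricted to participants with no antihypertensive start, stop or dose change before visit 3. Do not refill the excluded readings by LOCF. Report how many participants are excluded and in which direction their therapy changed.

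The cost is a change of wording and one extra analysis on data that Table 2 already collects. The sensitivity sample will be smaller, and it is selected, because therapy may be changed in response to BP itself. It shows how far the result depends on such changes and does not give an unconfounded effect.
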